**Fig. 6 Fig6:**
[figure not shown]
Sanitation map of Ingundu quartier (Draft version, June 2015), Sanitation map of ImpiniNsi quartier (Draft version, June 2015) - are correctly shown

All the 7286 households on the Sanitation Map will be assigned an identity number and marked with a color. They will be marked red when the household latrine does not improve, green when the latrine improves, and yellow when the latrine is under construction. The Sanitation Map can help the WASH committee as well as community members check the progress not only of the *quartier* they belong to, but also of the other groups. Community members will be educated on the herd protection effects of well-equipped latrines and also the importance of the 80% target for latrine coverage. If a *quartier* reaches 80% well-equipped latrine coverage, it will be certified as a ‘Healthy *quartier*’ and rewarded by the project implementer. The sanitation mapping is expected to create peer pressure within and among the *quartiers,* sparking ‘healthy’ competition that will expand the rate of coverage.

In addition, the Sanitation Calendar is to be used as an effective method of tracking diarrhea for a registered child. With the Sanitation Calendar, the incidence density of diarrhea can be calculated by dividing diarrhea cases by observed child numbers multiplied by the specific duration observed (e.g. week, month, etc.). This would be a more effective tool since it would cause less fatigue among the respondents, who would otherwise be asked to provide information about their children’s diarrheal episodes on a daily basis by interviewers. Assuming that the incidence of diarrhea among children is three times a year on average [32], the number of days marked ‘O’ in mothers’ diaries will not be very high. As for the duration of diarrhea, it was estimated at 10–20 days on average. Except for the days marked with ‘O,’ all the other days will be considered ‘X’. The Sanitation Calendar allows the day-to-day observation of diarrhea and resolves the limitations associated with the small number of clusters in the trial. Previous studies were unable to identify the effect of improved sanitation on diarrheal duration because they relied on the period prevalence of reported diarrhea. The utilization of the Calendar will enable us to explore a relationship between sanitation improvements and diarrhea and investigate the extent to which well-equipped and appropriately managed latrines affect disease duration. The measurement relying on caregivers’ reports, which are subjective in nature, is one of the limitations of this study. As we will not be able to conduct laboratory tests to assess children’s diarrhea incidence, there may be under-reporting or over-reporting of diarrhea. Despite this risk, we do not expect any significant difference of reporting patterns between the people of the intervention and control *quartiers*.

This trial is an efficacy trial because the focus is on proving the theory that universal sanitation coverage will reduce diarrhea, and thus, the interventions are designed to deliver high/universal latrine coverage with more certainty than an effectiveness trial implemented at scale [14, 15]. We intentionally developed a small-scale trial to ensure the successful results of sanitation promotion. There is a clear benefit to a small-scale project because the intensive execution of sanitation promotion is likely to be more effective in reaching the universal sanitation coverage in the setting of a small-scale project. Indeed, it has been reported that more sanitation promotion activities yielded success in small scale projects than in large scale projects [33]. However, the sufficient level of coverage is not always guaranteed in any circumstances, which represents another limitation of this study.

Sanitation coverage is defined as the proportion of households who have access to a well-equipped latrine that meets the six criteria specified by the UNICEF Healthy Village Programme in the DRC. In estimating the coverage, however, the access to communal latrines or using a neighbor’s latrine is excluded to focus on latrine usage at the household level. To avoid information bias or courtesy bias among the members of the WASH committee, the progress of latrine improvement will be observed and photographed with digital cameras provided to the WASH committee (June, 2015). Based on the photos taken by the committee, the supervisors will verify the improvement status. Two-meter-long sticks will be provided to the WASH committee to measure the depth of a pit. Latrine utilization will be assessed by the latrine condition, observing various elements such as odor, wet feces in the pit, a spider-web at the entrance, or a worn path to the latrine.

The degree of latrine improvement will be scored according to the well-equipped latrine criteria. This will allow us to assess whether and how the diminishing effect of well-equipped latrines on diarrhea incidence among children under four differs depending on the degree of latrine improvement. Previous studies [14, 15] exploring the health benefits of sanitation have not paid attention to the possibility that the effect of latrines might vary depending on the degree of their improvement. Although a recent trial [21] reported an increase in access to one’s own latrine from 33 to 64.8% in rural Mali, they found no effect of a community-led sanitation improvement on the children’s diarrhea. Based on the 5-f theory, the Joint Monitoring Programme defines an “improved sanitation facility as one that hygienically separates human waste from human contact,” highlighting the importance of accounting for improvement status of latrines. In the case of pit latrines, the existence of a slab and hand-washing facilities, pit-hole depth and number of flies could be considered criteria for identifying the improved status of latrines. Applying these criteria, the proportion of improved latrines in Pickering et al. (i.e., latrines with concrete slabs) would be reduced to less than 30%. Focusing solely on the presence or access to any latrine type may mask the genuine health benefits of improved latrines.

The study hypothesis was not disclosed to people subject to the trial, though the general objectives were explained to them when obtaining informed consent. Thus, people are highly unlikely to be aware of the arm to which they belong because the sanitation intervention will continue to be executed in the control arm during the second phase. We thus surmise that the underreporting of diarrheal prevalence among the caregivers with a household latrine will not be a serious problem in this study. However, the limitation of not blinding still remains in this study since having a latrine is explicit in itself and many of the WASH committee members in the control arms were aware of the intervention even from the beginning due to their participation in the community lottery activity for random allocation.

Since the trial’s randomization process yielded remarkably balanced results between the two arms, and since no other intervention is expected to roll out until February 2017, any differences observed in diarrheal incidence can be attributable to latrine improvement.

For this trial, keeping the Sanitation Calendar is crucial to documenting the progress toward the primary endpoint. A supervisory visit to the WASH committee will be made at least twice every month to encourage the mother or caregiver to record diarrheal incidence on a daily basis, in an unbiased manner. On this visit, the WASH committee will photograph the Sanitation Calendar to confirm whether it is being kept well, which will be verified by supervisors’ (WSA and SNHR sanitation experts) direct observations during the randomly sampled household visit. During the early stage of the intervention, in July and August 2015, strong emphasis will be placed on the importance of appropriately recording outcomes in the Sanitation Calendar. Accordingly the supervisory visit to randomly sampled households will be strengthened to help people get accustomed to recording in the Calendar in a desirable manner. The WASH committee will convene a community meeting to review the Sanitation Calendar on a regular basis and significant errors, if any, will be corrected.

Considering the alternative sanitation policies evaluation result [31], the non-discriminative distribution of material subsidies contingent upon voluntary preparation of some materials for latrine improvement and a commitment of labor may increase the uptake of well-equipped latrines within a short time period, with a strong social multiplier by increasing the ownership. This trial is expected to provide valuable information on the resource allocation of sanitation improvement by determining the effects of improved sanitation on diarrheal reduction for children. The findings of this study will be relevant to populations where improved water and sanitation coverage is minimal.

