### Primary health outcome

The primary outcome of the study is reduction in diarrheal incidence (cases per 1000 child-week), prevalence and average duration (days per episode) in children under four. To measure progress, the mother or caregiver of each household will record the diarrheal episodes of the youngest child under four on a daily basis using the ‘Sanitation Calendar’ (Fig. 4). The Sanitation Calendar will enable us to look into the intervention’s effects on incidence density as well as the duration of diarrhea in children under four. A 7-day recall period will be used to measure diarrheal prevalence.

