Assuming a coefficient of variation of 0.3 with 80% study power and 7.5% diarrheal prevalence in the intervention resulted in seven clusters (7 *quartiers*) per each arm. We increased the number of clusters to nine each in the control and intervention arm, and sampled 360 households in each trial arm. We will follow up at least 12 weeks to make 8640 child-weeks (‘child-weeks’ is the unit of the denominator) in each *quartier* as required to meet 80% power, considering a 12.5% loss to follow-up.

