### Project implementation

KECO will be responsible for supervision and management of the project implementation. Two sanitation experts have been deployed to this project team from the WSA to provide technical advice and three sanitation officials from SNHR have been seconded to facilitate community mobilization and provide information about the local culture, such as social norms and, if any, taboos during the project period.

Before the intervention, WASH committees were established right after 18 *quartiers* had been selected for the target area of the water supply program in February 2015; therefore, the committees were present in both the intervention and control arms. Nine WASH committee members were elected by the people living in each *quartier*. It was recommended that they elect at least three female members, but several *quartiers* could not recruit at least three female members to form their committee. The main roles and responsibilities of the WASH committee with regard to the water supply program are to maintain water facilities and collect water fees from the *quartier* residents. Later on, after 9 *quartiers* were selected for this sanitation intervention, we added new roles and responsibilities of the committee for latrine improvement for the intervention group and trained the committee members to perform those tasks. The new roles and responsibilities of the WASH committee are defined as (1) community mobilization on latrine improvement; (2) educating community people for healthier hygienic practices; (3) drawing and regularly updating the Sanitation Map; (4) monitoring the progress, especially on the ‘recording status of the Sanitation Calendar’ and ‘latrine improvement situation’ at the household-level in each *quartier*.

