### Health outcomes assessment, sanitation calendar

The incidence of the diarrhea of the youngest child under four will be recorded by the mother or caregiver on the Sanitation Calendar distributed to each registered household in early August, 2015. The mother or caregiver will be educated to mark ‘O’ whenever her youngest child under four has diarrhea and mark ‘X’ on each day without diarrhea over the next 12-month period of longitudinal observation. Mothers were informed of the definition of diarrhea - three or more of watery stools in 24 h, with pictures of various stool types produced by the World Health Organization.

Households will be monitored by the WASH committee twice a month and instructed to keep recording appropriately. We employed the diary methodology to overcome the limitations reported in previous studies, such as recall bias [29] and reporting fatigue, leading to underestimation [30]. The diary methodology will allow us to capture more precisely the effects of well-equipped latrines on the duration of diarrhea and diarrheal incidence density. As an incentive for keeping a diary, the project has made the Sanitation Calendar a voucher, which can later be exchanged with a gift. During the monthly monitoring visit, the WASH committee will check the status of diary recording by taking a photo of the Sanitation Calendar marked as ‘O’ or ‘X’ for each day of each month.

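### Diary days with no mark are coded as diarrhoea-free, which distorts incidence and duration and, if diary completeness differs by arm, the rate ratio

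*Protocol article*

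**What the plan says.** The section on the Sanitation Calendar under health outcomes assessment makes X an active mark. The mother enters O when the child has diarrhoea and X "on each day without diarrhea over the next 12-month period of longitudinal observation".

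The Discussion then states the analysis rule. Apart from days marked O, "all the other days will be considered" X. No exception is made for days that carry no mark. The same paragraph says that incidence density is obtained by "dividing diarrhea cases by observed child numbers multiplied by the specific duration observed".

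The Primary health outcome section ties two of the three primary measures to this diary: "The Sanitation Calendar will enable us to look into the intervention’s effects on incidence density as well as the duration of diarrhea". Prevalence, the third, is measured by 7-day recall there and again under Data analysis.

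Three other places bear on the point:
- The sample size section allows for dropout, "considering a 12.5% loss to follow-up".
- Project implementation says that "we added new roles and responsibilities of the committee for latrine improvement for the intervention group", and the list that follows includes monitoring whether calendars are being filled in.
- The Discussion says that community meetings will review the calendar and "significant errors, if any, will be corrected".

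**The concern.** Because a diarrhoea-free day has its own mark, the diary separates three states: O, X and not recorded. The Discussion collapses the last two. A family that stops recording for a month is then analysed as having had a healthy month.

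Blanks are to be expected. Recording is daily for 12 months, and the article itself names reporting fatigue as a known weakness of earlier work. The coding rule is stated outright, so it is not a detail left to an analysis plan that is not shown.

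At stake are the absolute incidence and duration figures. If the arms differ in how fully the diary is kept, the comparison on which the trial rests is also at stake.

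**Working it through.** **Inputs.** Control rate 0.10 and intervention rate 0.075 per child-week (Sample size calculation). Three episodes per child-year lasting 10–20 days (Discussion). Loss to follow-up 12.5% (Sample size calculation). Completeness by arm is not given anywhere, so every completeness value below is an assumption.

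**1. Planned effect.** 0.075 / 0.10 = 0.75, the stated 25% reduction.

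**2. Long blank spells coded X.** Let a share m of child-time be blank, in spells long compared with an episode and unrelated to illness. If that time stays in the denominator:

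- observed rate = true rate × (1 − m)
- observed ratio = true ratio × (1 − m_int) / (1 − m_ctl)

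| Complete, intervention / control | Factor | True 0.75 appears as | True 1.00 appears as |
|---|---|---|---|
| equal, any level | 1.000 | 0.75 | 1.00 |
| 90% / 80% | 0.90/0.80 = 1.125 | 0.84 | 1.13 |
| 80% / 90% | 0.80/0.90 = 0.889 | 0.67 | 0.89 |
| 95% / 80% | 0.95/0.80 = 1.188 | 0.89 | 1.19 |
| 80% / 95% | 0.80/0.95 = 0.842 | 0.63 | 0.84 |

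With 12.5% of child-time blank in both arms, the control rate of 0.10 is reported as 0.10 × 0.875 = 0.0875, and the ratio is unchanged.

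**3. Shorter spells.** The formula is a limiting case. Diaries were simulated for 4,000 children over 365 days, with three episodes a year and mean duration 10 or 20 days, and blanks were coded X. Blank spells of 28 days covering 10% of time multiplied incidence by 0.92–0.98, and covering 20% by 0.84–0.93, across two episode rules (an episode ends after one, or after three, consecutive non-O days). The incidences per 1000 child-weeks at 10% and 20% blank were 48.3 and 44.0, 47.2 and 44.5, 48.5 and 44.8, and 47.1 and 44.0. The 90%/80% factor is therefore 1.10, 1.06, 1.08 and 1.07. A true 0.75 appears as about 0.80–0.82, and the reverse split turns 1.00 into about 0.91–0.94.

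**4. Isolated blanks inside an episode.** These act the other way on the count. With 10% of days blank at random:

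| Episode ends after | Mean duration set | Episode count | Observed mean duration, days |
|---|---|---|---|
| 1 non-O day | 10 | ×1.69 | 9.7 to 5.2 |
| 1 non-O day | 20 | ×2.57 | 19.1 to 6.8 |
| 3 non-O days | 10 | ×1.02 | 9.9 to 8.8 |
| 3 non-O days | 20 | ×1.01 | 19.3 to 16.8 |

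The direction for incidence thus depends on the pattern of blanks. Scattered blanks shorten duration under either rule.

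**5. Dropout.** If 12.5% of children leave at a random time and their later days are coded X, incidence is multiplied by about 0.94–0.95. On average half of each leaver's year is lost: 1 − 0.125 × 0.5 = 0.94. This applies only if those days are counted at all.

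**The case against.** The best defence of the rule is that diarrhoea days are few and memorable. Mothers may mark every O and skip some X on healthy days. In that case the stated rule is unbiased, and counting only marked days is not. Three episodes of 10–20 days give 30–60 O days a year, leaving 335–305 healthy days. If 20% of those are left blank (assumed), 67–61 days drop out and 298–304 remain, so incidence is inflated by 365/304 = 1.20 to 365/298 = 1.22. This stands. It is a reason to run both codings, not to discard the difference between blank and X.

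The safeguards are also real: committee visits, photographs of the calendar, a gift voucher and supervisor checks. They may reduce blanks but do not change how a blank is coded.

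A reader might infer more than the article supports:

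- **That the arms are known to differ in diary monitoring.** Project implementation lists this among the roles added for the intervention group. The same list contains drawing the Sanitation Map, which the Discussion says is kept up in both arms, so the list does not show what control committees do not do. The accounts of household monitoring, photographs and review meetings are not limited to one arm. A difference is possible, not established.
- **That time after dropout is counted as healthy.** The denominator sentence, with its reference to observed time, can be read as excluding it. The 12.5% is only a sample size allowance.
- **That all primary measures are affected.** Prevalence comes from 7-day recall.
- **That diaries are rewritten at meetings.** The sentence on correcting errors may mean correcting how mothers record.

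**Conclusion.** The point holds. The coding rule in the Discussion conflicts with the recording instruction and turns non-recording into health in two primary measures, incidence density and duration. The article's figures do not allow the error in the rates to be sized, because completeness is not given and the direction for incidence depends on whether blanks come in spells or singly.

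Bias in the rate ratio is conditional on unequal completeness. Under the assumed 90% against 80% split, a true 0.75 appears as 0.84 with long spells and about 0.80–0.82 with 28-day spells. With the split reversed, no effect appears as 0.89 and about 0.91–0.94 respectively. These shifts matter against a planned reduction of 25%, but nothing in the article shows that they will occur. Whether dropout adds to the problem depends on how the coding sentence and the denominator sentence are reconciled.

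**What to change.** Replace the rule with three codes: O is diarrhoea, X is no diarrhoea, blank is missing. Then:

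- Base the primary denominator on recorded child-time and censor when the child leaves follow-up. State this so that the two Discussion sentences agree.
- Set in advance a maximum number of blank days that may be bridged within an episode. With no limit, two O days a month apart could merge into one episode.
- Report diary completeness by arm.
- Repeat the analysis with blanks coded X as a sensitivity analysis, because skipped X marks on healthy days bias the primary coding the other way.
- Keep the mothers' own marks where they have been photographed, and do not let later meeting corrections overwrite them in the primary analysis. The article does not say that photographs come before any correction, so this may not be possible for every calendar.

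The cost is slightly fewer child-weeks and one extra analysis. The marks and photographs are already planned.

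### The claims that reporting will not differ by arm, and that any difference in diarrhoea is due to latrines, conflict with the plan's own teaching, roll-out and diary procedures

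*Protocol article*

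**What the plan says.** All three primary outcomes come from the caregiver. Incidence and duration are taken from the daily Sanitation Calendar and prevalence from 7-day recall (Primary health outcome). The Discussion acknowledges the weakness: "The measurement relying on caregivers’ reports, which are subjective in nature, is one of the limitations of this study". It also says that laboratory confirmation is not possible.

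The Discussion then offers reassurance in three steps:

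- On the hypothesis: "The study hypothesis was not disclosed to people subject to the trial".
- On knowledge of allocation: "people are highly unlikely to be aware of the arm to which they belong because the sanitation intervention will continue to be executed". This refers to control quartiers in phase 2.
- On the consequence: "underreporting of diarrheal prevalence among the caregivers with a household latrine will not be a serious problem in this study". Earlier in the same section, comparing the two sets of quartiers: "we do not expect any significant difference of reporting patterns between the people of the intervention and control".

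The section adds that lack of blinding remains a limitation, because a latrine is plain to see and many control-arm committee members knew of the intervention from the lottery. It nevertheless closes the argument by crediting any difference in diarrhoeal incidence to latrine improvement. The reasons it gives are baseline balance and the absence of other interventions.

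Elsewhere in the Discussion, on the Sanitation Map: "Community members will be educated on the herd protection effects of well-equipped latrines and also the importance of the 80% target for latrine coverage". A quartier that reaches the target is certified "and rewarded by the project implementer".

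**The concern.** The outcome is a mark made, or an answer given, by a person who is not blinded. If the project has told that person that latrines prevent diarrhoea, and her quartier has just built them, she may leave mild or doubtful days unmarked. A lower reported rate in the intervention arm could then be partly or wholly a matter of reporting.

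The reassurance depends on caregivers knowing neither the hypothesis nor their arm, and the plan describes activities that work against both. At stake is the trial's main inference. The plan states in advance that a difference in diarrhoea may be read as the effect of latrines, and that step needs reporting to be equal between arms.

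**Working it through.** The point rests on text, and no printed figure of the plan is in dispute. The statements are set side by side first; an illustration of size follows.

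**1. Was the hypothesis withheld?** The Discussion describes an efficacy trial meant to show that universal coverage reduces diarrhoea, and the Background adds herd protection as the mechanism. The Sanitation Map paragraph has residents taught that same mechanism. Non-disclosure can therefore describe what was said at consent, but not what caregivers know while they fill in the diary.

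**2. Are people unaware of their arm?** Under Study design, the latrine programme runs only in the intervention arm for 8 months, and the second survey falls just before controls start. The promise of phase 2 does not hide who has the programme in phase 1. Once phase 2 is delivered, the arms no longer differ in programme. The Sanitation Map colours each household by latrine status, is kept in both arms, and lets residents see the progress of other quartiers. The Discussion itself concedes that a latrine is visible.

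**3. How could knowledge reach the diary?** Project implementation adds four roles to the committee for the intervention group; they include promoting latrines, hygiene education and monitoring the Calendar. The Discussion has the committee review the Calendar at community meetings, where significant errors are corrected. It also treats every day not marked O as X, so an omitted mark becomes a diarrhoea-free day. Calendar photographs and supervisor visits check that the diary is kept, not that an entry is true.

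**4. Does the attribution follow?** Baseline balance and the absence of competing programmes deal with confounding. Neither protects against measurement that differs after allocation.

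**5. Illustration of size (assumed).** Let u be the share of intervention-arm episodes that go unreported, with no true effect and full reporting in controls. The document gives no value for u. Inputs from Sample size calculation:

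- control rate 0.10 per child-week and planned reduction 25%;
- 9 quartiers and 360 households per arm, with 12 weeks of follow-up, so y = (360/9) × 12 = 480 child-weeks per quartier;
- coefficient of variation k = 0.063 or 0.30, both printed there.

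The apparent rate is λ₁ = 0.10(1 − u), and u/0.25 is the share of the planned effect imitated. With the plan's variance terms, SE = √{[(0.10 + λ₁)/y + k²(0.10² + λ₁²)]/9}, tested two-sided at 5% by the normal approximation.

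Example, u = 10% and k = 0.063: SE = √{[0.19/480 + 0.063² × 0.0181]/9} ≈ 0.0072, z ≈ 0.010/0.0072 ≈ 1.39, chance of significance ≈ 28%.

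| u (assumed) | Apparent ratio | Share of planned effect | Chance of significance, k = 0.063 | k = 0.30 |
|---|---|---|---|---|
| 10% | 0.90 | 40% | 28% | 10% |
| 20% | 0.80 | 80% | 82% | 29% |
| 25% | 0.75 | 100% | 95% | 43% |

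The first three columns only restate the assumption. The last two show that the result depends heavily on k.

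**6. What a negative-control item could show.** Assume a 10% item prevalence, 360 children per arm, one round and no clustering. For 10% under-reporting, z = 0.01/√[(0.10 × 0.90 + 0.09 × 0.91)/360] = 0.01/0.0219 ≈ 0.46, power about 7%. For 20%, z = 0.02/√[(0.10 × 0.90 + 0.08 × 0.92)/360] = 0.02/0.0213 ≈ 0.94, power about 15%. Clustering lowers both; pooling rounds raises them somewhat.

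**The case against.** The best defence is that the plan is open about the problem. It lists subjective reporting and lack of blinding as limitations, and says diarrhoea may be under- or over-reported. A reader might infer that it overlooks reporting bias, and the text does not support that. What stands is narrower: the limitations are stated and then left out of the conclusion.

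Four other stronger readings also go too far:

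- **The teaching is given to one arm only.** The Discussion does not say so, and the Sanitation Map runs in both arms. Teaching shared equally need not by itself create an arm difference. However, the first-phase roll-out and the added committee roles place latrine promotion in the intervention arm, so the question is open.
- **The reward pays for low diarrhoea counts.** It is tied to latrine coverage, and the only diary incentive described is a gift for keeping it. Any pull on reporting is indirect.
- **The lots were drawn in public.** The text speaks of leaders choosing envelopes and of a community lottery; it does not say who watched.
- **Nothing in the plan bears on reporting bias.** Fly counts, observed faeces, supervisor visits and the analysis of children in households without latrines allow some triangulation. None verifies the truth of a diary entry.

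The case against negative-control items also has force. They have low power, are not specific to diarrhoea, and test recall rather than the diary. Toothache suits children of about 20 months poorly, and scrapes could change with construction work. This limits what such items can show, but does not make them useless as a one-directional warning.

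**Conclusion.** The point holds as an internal contradiction with a consequence for inference. The stated grounds for expecting equal reporting are undercut by the plan's own procedures, so crediting any difference in diarrhoea to latrines does not follow for an unblinded, caregiver-reported outcome.

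The document gives no basis for the size of any bias. The illustration shows what assumed under-reporting would do: at 10% confined to one arm, it imitates 40% of the planned effect and gives roughly a 10% to 28% chance of a significant result against a nominal 5%, depending on k. A reader might infer that the trial's estimate will be biased by some such amount. The documents support only that a false or exaggerated effect can arise and that the plan has no sound reason to exclude it. The correction should be made, because it changes what the trial may conclude and costs almost nothing.

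**What to change.** In the Discussion:

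1. Limit the non-disclosure statement to what was withheld at consent, and note that residents are later taught about herd protection.
2. Withdraw the claims that people are unlikely to know their arm and that no reporting difference is expected.
3. Replace the sentence crediting any difference in incidence to latrines with a conclusion qualified for differential reporting, to be read alongside the fly counts and observed faeces.

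In any survey round still to come, add in both arms one or two caregiver-reported 7-day items that suit children of about 20 months and are not plausibly changed by latrines, hand-washing or construction work. State in advance that an arm difference on these items signals reporting bias, and that no difference does not rule it out, for the reasons of power, specificity and recall given above.

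The cost is protocol wording and about a minute more per interview. The last scheduled round is February 2017, before the article's publication date. If the rounds are complete, the wording changes and the qualified conclusion still apply.
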